### Data handling and confidentiality

Data will be collected electronically using tablets. The safety and confidentiality of the data will be ensured. Data will be backed up regularly. Names or identities of participants will be unidentifiable and will not be used in any publication. Only the “research teams”, DCC and WHO will have access to data. The paper-based log books / registers will be retained for 10 years and then destroyed.

### Data management

RTI has developed the PSBI data management system using the Tangerine software platform (see http://www.tangerinecentral.org/ and https://docs.tangerinecentral.org/). RTI will run quality checks to identify missing data and will harmonise the data across sites, within sites and with WHO. It will provide monthly reports and data to WHO for administrative and supportive purposes. They will also provide data and frequency tables and trends to Data Safety Monitoring Board (DSMB) or the Technical Advisory Group (TAG) for overall monitoring purposes as required.

### Data analysis

Simple comparisons of means and proportions by intervention and control treatment arms will be carried out to evaluate the baseline comparability of the two groups. The Kolmogorov-Smirnov test of normality will be used to test the normality of the data. The primary analyses will be per-protocol to compare treatment outcomes by comparing proportions of poor clinical outcomes (including deaths and deterioration) between intervention and control arms using the Chi-square test, setting statistically significant as *P* <0.05. An intention-to-treat analysis will also be conducted. The clinical outcomes between control and intervention treatment arms will be compared, and the difference in the risk of poor clinical outcomes together with 95% confidence intervals, will be calculated. Secondary analyses will be performed to identify predictors of poor clinical outcomes.

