**Methods:**

A multi-centre, individually randomised, open-label trial will be conducted in seven sites in six countries: Bangladesh, Ethiopia, India (two sites), Nigeria, Pakistan and Tanzania. A common protocol will be used with the same study design, including the participants, intervention, comparison, outcomes, quality control, and analysis procedures. 0-59 days old infants presenting with moderate-mortality risk signs (low body temperature (<35.5°C), movement only when stimulated, stopped feeding well) or two or more signs of clinical severe infection (CSI) will be assessed and pre-enrolled. After 48 hours of hospital stay, clinically stable infants with a negative C-reactive protein test will be randomised either to hospital discharge on oral amoxicillin (intervention) or continued hospitalisation (control) arm. The intervention arm will receive oral amoxicillin for five days, whereas the control arm will receive injection gentamicin plus injection ampicillin for five more days plus supportive therapy if needed. We plan to enrol 5250 eligible young infants, 2625 infants in each of the two study arms. An experienced, well-trained independent outcome assessor will visit all enrolled cases on days 4, 8 and 15 after the initiation of treatment to assess the study outcomes in both intervention and control arms. The primary outcome of poor clinical outcome defined as death between randomisation and day 15 of initiation of treatment, deterioration during the 7-day treatment period, or persistence of the presenting sign of CSI at the end of the 7-day treatment period will be compared to assess if an early discharge and outpatient treatment leads to superior or at least non-inferior clinical outcome than continued inpatient treatment. The harmonisation of activities, including methods and processes, will be carried out diligently. Central training will be conducted by the WHO coordinating team, a central data coordination centre to collate all data, standardisation exercises for all clinical signs and internal and external monitoring. All the selected sites have extensive research experience. Through regular online and physical meetings, data-based monitoring, and physical site visits by WHO monitors, quality assurance and harmonisation will be ensured. This trial has been approved by the WHO and local site institutional ethics committees.

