### Outcome assessment

Due to the nature of the treatment, the trial cannot be blinded. To reduce potential measurement bias, we will use Independent Outcome Assessors (IOA) who will not be associated with the treatment of the infant. The IOAs who will be the Outcome Assessment Team members will conduct outcome assessment visits using the designated days four, eight and 15 post-admission. In the hospital arm, the outcome visits on day four will be done in the hospital, while on days eight and 15, visits will be done at home (or in the hospital or where ever the infant may have moved to). In the outpatient arm, the outcome visits on days four, eight, and 15 will be done at home or where ever the infant may have moved to. If the infant is not able to be seen on the specified day, then a window of additional time will be allowed for outcome follow up, i.e. for day four visit, an additional 24 hours; for day eight and day 15 visits, an additional 48 hours. The outcome team will continue to visit the family during this time window to complete these visits.

Outcomes will only be ascertained by the IOAs per the criteria mentioned above under outcomes. A case will be considered to have a poor clinical outcome if it is confirmed by the IOA.

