### Follow-up

All infants will be followed up till day 15 after the initial admission. Infants in the intervention arm will be asked to return to the hospital for treatment and assessment by the hospital physician / nurse on day five of treatment initiation. Infants will be assessed for the presence of any adverse event during scheduled follow-up visits to the hospital OPD, hospital visits by the family for care-seeking at any time during the follow-up period, or reported to the IOA team during a home visit and referred for care. These will be managed by the treating physician as per routine practice and followed up till resolution.

Infants in the control arm will be followed up and managed as per routine hospital procedures.

All efforts will be made to follow all the enrolled young infants in both studies. If a young infant does not come to the hospital / health facility on the follow-up day, the study team will contact them by phone and counsel parents / caregivers to bring the infant to the hospital / health facility. Transportation costs will be provided to families of all patients if needed.

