### Withdrawal from the study

Parents / caregivers can withdraw at any time after enrolment, and those who withdraw at any stage from the study will continue to receive free-of-charge standard treatment and treating physicians will follow them as per hospital standard procedures. These cases will be excluded from the per-protocol analysis but will be included in the intention-to-treat analysis.

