### Non-enrolled cases

All non-enrolled cases who will be excluded during re-screening after 48 hours of initial screening and critically ill cases will be followed up on Day-15 after the initial screening to obtain information about their survival status. Consent will be obtained from them about collecting this information. The survival status of each non-enrolled infant will be collected either through a home / hospital visit (wherever the infant will be present) or by calling his / her parents / caregivers. This information will be used for the secondary analyses.

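### Per-protocol is the only primary analysis in an open-label non-inferiority trial and drops every withdrawn infant; ITT should be co-primary, and outcome follow-up after withdrawal should be made explicit

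*Protocol article*

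**What the plan says.** The Data analysis section makes one analysis set primary: "The primary analyses will be per-protocol to compare treatment outcomes". It then adds: "An intention-to-treat analysis will also be conducted". Nothing in the article requires the two to agree.

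The section Withdrawal from the study lets families withdraw at any time after enrolment and says of them: "These cases will be excluded from the per-protocol analysis but will be included in the intention-to-treat analysis". It draws no distinction by reason. On what happens next, it says only that "treating physicians will follow them as per hospital standard procedures".

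Three other sections bear on whether those infants' outcomes are known. Outcome assessment reserves the judgement to the independent outcome assessors (IOA): "A case will be considered to have a poor clinical outcome if it is confirmed by the IOA". Follow-up states: "All efforts will be made to follow all the enrolled young infants in both studies". Patient safety promises each enrolled infant a day-15 assessment and makes no exception for withdrawals.

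The Sample size section sets the margin at an RR of 1.40, one-sided alpha at 0.025, and one overall figure of 10% for loss or withdrawal. The research question asks about non-inferiority only, but the Methods part of the Abstract asks whether early discharge "leads to superior or at least non-inferior clinical outcome than continued inpatient treatment".

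**The concern.** Per-protocol analysis has a proper place in a non-inferiority trial. The weakness is that it stands alone as primary. Excluding infants for something that happens after randomisation breaks the randomised comparison if the excluded infants differ between arms, and families here know their arm.

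The design gives a reason to expect such a difference. All randomised infants are clinically well and CRP-negative on day 3. One arm then goes home and the other is asked to stay five more days. The Discussion argues that families with limited resources cannot manage long stays, because of lost wages, added costs and other children at home. That reason for leaving acts mainly on the control arm. Home-arm families may withdraw for other reasons, and the infants concerned may have a different prognosis.

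At stake is a claim that early discharge is non-inferior, or even superior, resting on a subset that randomisation no longer protects.

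**Working it through.** **The plan's own power figure.** Inputs from Sample size: 2625 per arm, 10% loss (2362 per arm), margin RR 1.40, one-sided alpha 0.025, no true difference. On the risk-difference scale, power = Φ(0.40p / √(2p(1−p)/n) − 1.96).

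- p = 5%: 0.020 / √(0.095/2362) = 0.020/0.00634 = 3.154; Φ(1.194) = 88.4%, as in Table 3.
- p = 7.5%: 97.5%, as in Table 3.

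**Illustration 1: arms truly equal (assumed inputs).** Both arms at 5%; 15% of control and 3% of home infants withdraw; risk in those withdrawn is 10%.

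- Control per-protocol risk = (0.05 − 0.15×0.10)/0.85 = 4.12%.
- Home per-protocol risk = (0.05 − 0.03×0.10)/0.97 = 4.85%.
- Per-protocol RR = 4.85/4.12 = 1.18, although the true RR is 1.00.

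**Illustration 2: home truly worse by the full margin (assumed inputs).** Control 7.5%, home 10.5%, true RR 1.40; 5% of control and 15% of home infants withdraw, with twice their arm's average risk.

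- Control = 0.075(1 − 0.05×2)/0.95 = 7.11%.
- Home = 0.105(1 − 0.15×2)/0.85 = 8.65%.
- Per-protocol RR = 1.22.
- SE of log RR, with n = 2625×0.95 and 2625×0.85: √((1−0.0711)/(2494×0.0711) + (1−0.0865)/(2231×0.0865)) = 0.0999.
- Chance of claiming non-inferiority = Φ((ln 1.40 − ln 1.217)/0.0999 − 1.96) = Φ(−0.557) = 28.9%, against a nominal 2.5%.

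**Range.** Same method, 7.5% control risk, 10% withdrawal overall when averaged across arms; h is the risk in withdrawn infants relative to their arm's average.

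| Withdrawal, control/home | h | Per-protocol RR if true RR is 1.40 | False non-inferiority | Power if true RR is 1.00 |
|---|---|---|---|---|
| 10% / 10% | 0.5, 1, 2 | 1.40 | 2.5% | 92.4%, 90.9%, 87.1% |
| 15% / 5% | 0.5 | 1.32 | 9.4% | 97.8% |
| 15% / 5% | 1 | 1.40 | 2.5% | 90.8% |
| 15% / 5% | 2 | 1.61 | 0.04% | 43.2% |
| 5% / 15% | 0.5 | 1.48 | 0.5% | 80.0% |
| 5% / 15% | 1 | 1.40 | 2.5% | 90.8% |
| 5% / 15% | 2 | 1.22 | 28.9% | 99.1% |

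ITT with every outcome observed gives 2.5% and 93.5% throughout. Bias in per-protocol needs withdrawal that is related to outcome and also differs by arm. Equal rates are not enough if prognosis differs: 10% in each arm with h = 1 in control and h = 3 at home gives RR 1.09 and 71% false non-inferiority, an extreme case.

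**Cost of requiring both sets.** Take 2362 per arm in per-protocol, 2625 per arm in ITT with all outcomes observed, and the same true risk in both. The two test statistics then have correlation √(2362/2625) = 0.949. On the risk-difference scale that reproduces Table 3, joint power is 87.3% at 5% (88.4% for per-protocol alone) and 97.2% at 7.5% (97.5% alone).

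**The case against.** The strongest reply is that per-protocol is an accepted analysis for non-inferiority, that ITT is already planned, and that nothing in the article says withdrawal will differ by arm. Families give a second consent at enrolment knowing that either arm is possible, and Sample size uses one 10% rate. This stands as far as it goes: differential withdrawal is an expectation, not a documented fact. The reason given in the Discussion also points to more leaving in the control arm. In that direction, higher-risk leavers make non-inferiority harder to show, as in Illustration 1; lower-risk leavers make it easier (9.4% in the table). The 29% case needs more withdrawal from the home arm.

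Stronger readings are tempting but unsupported. A reader might infer that withdrawn infants leave assessor follow-up. The withdrawal section names only treating physicians but does not say assessor visits stop, and Follow-up and Patient safety point the other way. A reader might also infer that a withdrawn infant's events count as no event because no assessor confirmed them. Outcome assessment says who confirms an outcome, not how a missing one is handled, and that rule may sit in an analysis plan not shown. Hence it cannot be said that both analysis sets are biased as written. Nor does the article say that worsening removes an infant from the per-protocol set: the only exclusion it states is withdrawal by the family.

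Finally, superiority appears in the Abstract but not in the research question, and no section assigns a superiority test to per-protocol. It is a secondary reason for the change.

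**Conclusion.** The point holds in a limited form. Per-protocol is the sole named primary analysis of an unblinded non-inferiority trial, and all withdrawals after randomisation leave it regardless of reason. That comparison is open to bias in either direction if withdrawal differs between arms in rate or prognosis and is related to outcome.

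Under the assumed splits of a 10% overall rate, with the same h in both arms, false non-inferiority ranges from 0.04% to about 29% against 2.5%, and power at equality from 43% to 99%. With equal rates and equal prognosis, the per-protocol RR is unbiased. These figures show sensitivity; they do not forecast this trial.

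ITT gives the protection shown only if withdrawn infants' outcomes are actually known. On that the sections on withdrawal, outcome assessment, follow-up and patient safety are not reconciled. This is an ambiguity to settle, not a demonstrated loss of data.

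**What to change.** 1. Make ITT (all randomised infants, as allocated) co-primary with per-protocol. Claim non-inferiority only if the upper confidence limit of the RR is below 1.40 in both.
2. Base any superiority claim on ITT alone.
3. Reconcile Outcome assessment, Follow-up, Patient safety and Withdrawal from the study. Separate stopping study treatment from withdrawing from follow-up. State that, where families agree, the independent assessor still ascertains day-8 and day-15 outcomes. At a minimum, apply the check already planned for infants excluded at re-screening, who "will be followed up on Day-15 after the initial screening to obtain information about their survival status".

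The cost is wording in the protocol and analysis plan, a line in the consent form, and the follow-up visits or calls for withdrawn infants where not already made. Both analyses are already planned. Requiring both to succeed needs no alpha adjustment; the price is the power loss of about one percentage point at 5% incidence derived above.

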Several countries have adopted the WHO PSBI guideline [5]. The safety and effectiveness of simplified outpatient therapy for PSBI have been shown through implementation research in several countries in Africa and Asia when hospitalisation is not feasible [10-21]. In the first two months of life, 8-10% of infants can have an episode of PSBI, whereas only 25-50% of them may reach a hospital for treatment in low and middle-income countries (LMICs). However, hospitalisation has innate risks, e.g. multi-drug resistant nosocomial infection [22-25], so only those sick young infants with PSBI signs should be hospitalised who have a favourable benefit-risk ratio. Secondary analysis of African Neonatal Sepsis Trial (AFRINEST) data [6,7] showed that those young infants with movement only on stimulation, not feeding well or low body temperature (<35.5^°^C) have a much higher case fatality risk (CFR) of 3.2%, 4.0% and 11.0%, respectively than those with high body temperature (>38^°^C), severe chest indrawing, or fast breathing (>60 breaths per minute in 0-6 days old infants), who had a CFR of 0.8%, 0.9% and 2.0%, respectively [26]. Infants presenting with two or more signs of CSI also had a relatively moderate risk of mortality (CFR = 5.7%). As expected, signs of critical illness were associated with a very high risk of death (convulsions (11.3%), unable to feed at all (22.9%) and no movements at all (25.0%)) [26].

An important inference from these findings is that infants with moderate mortality risk signs of CSI (stop feeding well, movements only on stimulation, low body temperature), multiple signs of CSI, as well as those with a critical illness [26] are likely to benefit from hospitalisation. In contrast, young infants with low mortality risk signs of CSI (severe chest indrawing, temperature >38^°^C or fast breathing with >60 breaths per minute in 0-6 days old) may not need inpatient treatment in a hospital. Additionally, analysis of AFRINEST data by place of treatment showed that CFR was three times higher (6.5%) in hospitalised young infants compared to those treated on an outpatient basis (1.9%) when they refused referral for the same signs of CSI [26]. This could be because they were either sicker, received sub-standard care at the hospital, or developed a nosocomial infection.

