### Screening and enrolment

Young infants up to two months of age at the outpatient or emergency department will be examined, triaged, and stabilised by the consulting paediatrician or physician of the participating hospital. This process followed as part of regular facility procedures is referred to as “pre-screening”. If the paediatrician / physician observes signs of CSI during their initial assessment and the clinical condition of the infant is stable, the infant will be assessed by the study screening, enrolment and randomisation team. Screening of sick young infants will be performed by a study nurse / physician in the outpatient or emergency department of the participating hospital, and information will be captured on the case report form (screening and pre-enrolment form). Those who fulfil the above-mentioned inclusion criteria and do not have any exclusion criteria will be pre-enrolled after confirmation of clinical signs by the treating physician. The study nurse / physician will fill out the appropriate case report form at this stage. Infants who are not eligible for enrolment will be managed as per the treatment protocols of the hospital. All young infants with any moderate-mortality-risk sign or two or more signs of CSI (**Box 1**) will be admitted for injectable antibiotics by the treating physician. The CRP blood test will be conducted 48 hours post-admission. The study screening, enrolment and randomization team will re-screen the admitted infant using an appropriate case report form to assess the infant’s status and eligibility for the trial. Infants will be enrolled in the trial if they are clinically well at the time of the visit (none of the PSBI signs) and have a CRP <10 mg / l. However, if the treating physician has any concerns or reasons for wanting the child to remain in the hospital, then the child will not be considered for randomisation and will be excluded from the study.

See the study approach for screening, enrolment and randomisation in **Figure 1** and the implementation strategy in **Table 2**. In addition, study information regarding objectives and procedures will be posted in the labour and delivery wards, antenatal care clinics and postnatal clinics in the participating hospitals.

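### The primary test is an unadjusted chi-square on the per-protocol set; pre-specifying adjustment for presenting sign, already recorded before randomisation, would be a small, low-cost improvement.

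*Protocol article*

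**What the plan says.** **Primary method.** The Data analysis section states: "The primary analyses will be per-protocol to compare treatment outcomes". The method is "comparing proportions of poor clinical outcomes (including deaths and deterioration) between intervention and control arms using the Chi-square test", with significance set at P < 0.05. An intention-to-treat analysis is added. On the effect measure it says that "the difference in the risk of poor clinical outcomes together with 95% confidence intervals, will be calculated". No covariate or stratum is named for the primary comparison. Baseline variables reappear only in this sentence: "Secondary analyses will be performed to identify predictors of poor clinical outcomes".

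**Presenting sign.** Under Participants, entry requires any moderate-mortality risk sign, or two or more signs of clinical severe infection. Under Screening and enrolment, "information will be captured on the case report form (screening and pre-enrolment form", and this happens before admission and so before randomisation. The section on randomisation describes 1:1 allocation in blocks of four, six and eight, with one set of codes per hospital. It does not name presenting sign as a stratum.

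**Evidence that sign is prognostic.** The introduction reports, from a secondary analysis of an earlier African trial, that infants with movement only on stimulation, poor feeding or low temperature "have a much higher case fatality risk (CFR) of 3.2%, 4.0% and 11.0%, respectively". Infants with two or more signs had a case fatality of 5.7%.

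**Margin.** The Sample size section sets a relative risk of 1.40 as the non-inferiority margin. Table 3 gives power of 96.6%, 97.5% and 88.4% at control incidences of 10.0%, 7.5% and 5.0%.

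**The concern.** The entry criterion is itself a candidate prognostic variable. It is known for every infant before allocation and costs nothing more to collect. A two-by-two chi-square leaves it out. Any difference between arms in the share of higher-risk signs then stays in the estimate, and the variance that sign could explain stays in the interval.

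This matters somewhat more because the primary set is per-protocol. The section on withdrawal removes withdrawals from that set. Parents know the arm, and one arm stays in hospital for five more days, so exclusions could differ between arms and with severity. Balance by randomisation is not assured after such exclusions.

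What is at stake is a small shift in the point estimate and a slightly wider interval than necessary. The validity of the test is not at stake.

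**Working it through.** **1. Inputs.** From the article: 2625 per arm, 10% loss, so n = 2625 × 0.9 = 2362.5 evaluable per arm; one-sided α of 0.025; margin RR 1.40; control incidence p of 5%, 7.5% or 10%; case fatality by sign 3.2%, 4.0%, 11.0% and 5.7% (two or more signs). Assumed, because the article does not give them: the shares of the four groups, and that the groups do not overlap.

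**2. The plan's own power.** Unadjusted risk-difference formula with true RR = 1: power = Φ(0.4p / √(2p(1−p)/n) − 1.96).

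- p = 5%: 0.020 / 0.00634 = 3.154; Φ(1.194) = 88.4%. Matches Table 3.
- p = 7.5%: Φ(3.915 − 1.96) = 97.5%. Matches.
- p = 10%: Φ(4.583 − 1.96) = 99.6%, against the stated 96.6%. This cell does not reproduce on the formula that gives the other two; that is a separate matter.

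The two matching cells come from an unadjusted formula, so the planned power does not depend on adjustment.

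**3. Variance explained by sign.** R² = Σw(r − m)² / [m(1 − m)], where w are the shares, r the risks in the order above, and m = Σwr. The adjusted standard error is about √(1 − R²) times the crude one.

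| Assumed shares | m | R² | Equivalent infants (5250 × R²) | Power at 5% |
|---|---|---|---|---|
| 0.20 / 0.50 / 0.10 / 0.20 | 4.88% | 1.04% | 55 | 88.7% |
| 0.15 / 0.35 / 0.25 / 0.25 | 6.06% | 1.56% | 82 | 88.9% |
| Equal | 5.98% | 1.64% | 86 | 88.9% |
| Most favourable: 64% at 3.2%, 36% at 11.0% | 6.01% | 2.48% | 130 | 89.1% |

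Example (equal shares): 3.154 / √(1 − 0.0164) = 3.180; Φ(1.220) = 88.9%. The gain over 88.4% is 0.3 to 0.8 points. It is smaller at higher incidence: at equal shares, 97.5% becomes 97.7% and 99.56% becomes 99.61%.

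With the same relative spread rescaled to a 5% mean, R² is 1.4% (equal shares) to 2.3% (most favourable), and power is 88.8% to 89.1%.

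**4. Simulation.** 20,000 trials, 2362 per arm, equal shares, risks rescaled to a 5% mean. Power was 88.2% crude and 88.8% stratified (Mantel-Haenszel risk difference), with a variance ratio of 0.984. The two-sided type I error of the test of no difference was 4.9% for both.

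**5. Chance imbalance.** Assume 10% of infants have low temperature. The SD of the between-arm difference in share is √(2 × 0.1 × 0.9 / 2362) = 0.87 points. A 2-SD imbalance (1.75 points) times a risk gap of 11.0 − 4.0 = 7 points moves the risk by 0.12 points. That is 0.12 / 5 = 2.4% on the RR. Against a standard error of 0.634 points it is 0.19 SE.

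**6. Per-protocol imbalance (illustration only).** If exclusions left a 3 to 5 point difference in the low-temperature share, the shift would be 0.21 to 0.35 points, or about 4% to 7% on the RR at 5% incidence.

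**The case against.** The strongest case against acting is that nothing here is wrong. In a concealed, individually randomised 1:1 trial the unadjusted comparison keeps its type I error, and its interval already allows for chance imbalance. A 2.4% shift on the RR is small beside an interval whose upper limit lies about 28% above the estimate (exp(1.96 × 0.127) = 1.28). Covariates are often settled in an analysis plan, which is not shown. All of this stands. What remains is that the article does name a primary method, and that method has no covariate, so a later adjusted primary analysis would depart from it.

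The evidence on sign is also indirect. A reader might infer that presenting sign separates the risk of this trial's primary outcome from 3.2% to 11.0%, or that it is the main prognostic factor among the randomised infants. The article supports neither.

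- The figures are deaths counted from presentation in an earlier trial. The outcome here is a composite that includes later clinical signs.
- Only infants free of every sign at 48 hours and with a negative CRP are randomised. In that earlier trial's outpatient-treated infants, 39.7% of deaths fell in the first 48 hours.
- For infants recovered at 48 hours the article gives one figure, 0.4% mortality from day 3 to day 15, not split by presenting sign. Its only graded predictor of later death is status at 48 hours (0.4%, 0.7% and 8.0%), which eligibility already restricts.

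Finally, the sign groups overlap under the entry criteria, so the four-group calculation is only a guide.

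**Conclusion.** The point stands as a low-priority improvement. The article fixes an unadjusted primary test on a per-protocol set while a plausible prognostic variable is already in hand and unstratified. With the case fatality risks taken at face value and assumed shares, adjustment explains about 1.0% to 2.5% of outcome variance and adds about 0.3 to 0.8 points of power at 5% incidence. The true gain is probably smaller after the 48-hour and CRP filter.

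A reader might go further and conclude that the planned test is invalid or that the trial is underpowered without adjustment. Neither follows: type I error is held under randomisation, and the stated 88.4% at 5% incidence is itself an unadjusted figure.

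The better argument is protection in the per-protocol set, but its size is unknown, and adjustment removes only the imbalance carried by the measured sign. Other selection through exclusions would remain.

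**What to change.** Pre-specify the primary estimate as the marginal relative risk (intervention versus control) with its 95% confidence interval, the upper limit compared with 1.40. Obtain it from logistic regression with standardisation, or from modified Poisson regression with robust variance. Include arm and mutually exclusive presenting-sign categories taken from the screening form, for example: low temperature present; another single moderate-risk sign; two or more signs without low temperature. Apply the same model in the per-protocol and intention-to-treat sets, and show the unadjusted proportions as support. An age term is optional, since the article gives no risk by age group.

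**Cost.** A sentence or two in the analysis section, a few lines of code, and the sign categories defined before data are seen. No new data are needed.

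**To state openly.** The matching power figures in Table 3 are on the risk-difference scale. Tested on the log relative risk, unadjusted power at 5% incidence is Φ(ln 1.40 / 0.1268 − 1.96) = 75.6%, and adjustment lifts it to at most 76.6%. That difference comes from the scale on which the margin is tested, not from adjustment, and should be settled with the sample size.
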